### Ethics, study registration and consent

This trial was approved by independent ethics committees at both participating institutions: the University Hospital Hradec Králové (registration number 201308 S27P) and the University Hospital Olomouc (registration number 129/13). The DRAPA trial will be conducted in the context of Good Clinical Practice and in accordance with the Declaration of Helsinki. The trial is registered at ClinicalTrials.gov under the registration number NCT01988519. All patients who are scheduled for pancreatic resection in participating institutions will be screened for eligibility and informed in detail about the DRAPA trial. Informed consent will be obtained from each participant. The study procedures, risks, benefits and data management will be clarified with the patients before they are asked to give their informed consent to participate.

### Study treatment

The surgical technique is standardized in both participating institutions and has been described previously [2]. Standard resection of the pancreatic head with duodenum is performed, followed by the reconstruction phase. A jejunum limb is prepared and brought through the transverse mesocolon for the pancreatic and biliary anastomosis. Pancreaticojejunostomy is performed in end-to-side fashion. No stents are used. No additional manipulation, such as fibrin glue or reinforcement with meshes, is allowed. The end-to-side hepaticojejunostomy is made in a single layer of interrupted stitches about 15 cm distal from the pancreaticojejunostomy. End-to-side duodenojejunostomy is performed about 50 cm distally in the antecolic position. For distal pancreatectomy, after exploration of the abdominal cavity, the pancreas is exposed and transected by scalpel in a fish mouth fashion. A splenectomy is performed according to the surgeon’s discretion based on the benign or malignant nature of the tumour. The main pancreatic duct is occluded with a crossing stitch. The pancreatic remnant is then closed with interrupted stitches. In pancreaticoduodenectomy, two drains are placed: one in front of and one behind the pancreatic anastomosis. In distal pancreatectomy, one drain is placed near the pancreatic remnant. A second drain is placed in the left subphrenic area only when splenectomy is performed.

In patients assigned to the closed passive gravity drainage group, passive tube drains (pfm medical, Cologne, Germany) are used. In patients assigned to the closed-suction drain group, BLAKE silicone drains (Ethicon Endo-Surgery, Cincinnati, OH, USA) are used. Drains are pulled through a separate stab incision outside the laparotomy and fixed with a stitch to the skin. The volume of the fluid is measured every 24 hours and noted in the patient’s record form. Amylase content in the drain fluid is analysed every other day starting on the third postoperative day until removal of the drain. Drains are removed between day 4 and day 6 after the surgery if no POPF develops.

### Safety aspects

Pancreatic resection is a highly technically demanding procedure. High-volume surgeons with great experience have better results than low-volume surgeons with less experience [34]. In order to avoid bias based on the learning curve of the surgeons, every surgical procedure will be performed or supervised by a senior surgeon who has experience with at least 50 pancreatic resections. Insertion of both types of drain is a simple common procedure performed on a routine basis, and no special training is necessary and no complications are expected.

### Postoperative data collection

A daily visit of the study patients will be made by clinical investigators or a delegated physician. All protocol-required information collected during the trial will be entered into the patient’s record form. Preoperative data gathered include patient sex, age, body mass index, American Society of Anesthesiologists physical status classification system score and comorbidities, especially those considered to increase the risk of POPF (diabetes mellitus and ischaemic heart disease) [35,36]. Intraoperative data to be collected include surgery duration, estimated blood loss, diameter of the main pancreatic duct and pancreatic gland texture. The diameter of the main pancreatic duct will be measured with a set of probes. Postoperative data to be gathered include volume of the drain output measured every 24 hours, amylase content analysed every other day starting on day 3, and the day of drain removal. Laboratory tests will include serum amylase, C-reactive protein, bilirubin and leukocyte count on days 3 and 7 [37]. Postoperative course assessments will include duration of intensive care, hospital stay including readmissions for postoperative complications, reinterventions (reoperations, endoscopy and interventional radiology procedures) and the reasons for readmissions. All the patients will have undergo ultrasonography or computed tomography (CT) before discharge from the hospital to detect any fluid collections. The patients will be seen by a clinical investigator 6 weeks and 3 months after the surgery in the outpatient department.

### Primary and secondary endpoints

The primary endpoint of this study is the rate of POPF occurrence. POPF is defined by the ISGPF as any measurable volume of drain fluid on or after postoperative day 3 with amylase content greater than three times the normal upper serum value [6]. Three grades of POPF are determined according to clinical severity: A, B and C.

Grade A POPF, also called ‘transient fistula’, has no clinical impact. The patient’s clinical condition is good, and little or no change in clinical management is required. Hospital discharge is not delayed. The drains are usually removed within 3 weeks.

Grade B POPF is symptomatic and clinically apparent, and peripancreatic collections may occur. Changes in clinical management are required, such as nutritional support, as well as antibiotics in cases of infection, and new drains into the collections may be inserted. Hospital stay is usually delayed, or readmission may be required.

Grade C POPF is severe and clinically significant. The clinical condition of the patient is poor, and stability may be borderline. Major changes in clinical management are required, such as intensive care, CT-guided drainage of peripancreatic collections or reoperation.

The secondary endpoint is the postoperative morbidity, including wound infection, intraabdominal collections, delayed gastric emptying, postoperative haemorrhage, pneumonia, abdominal rupture, cardiac events and neurological complications (Table 1), as previously defined [5,30,38-41]. Postoperative complications are graded based on severity according to the Clavien-Dindo definition as modified by DeOliveira and colleagues for pancreatic surgery [42,43] (Table 2).

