Recent studies show that the use of drains might not be beneficial for the patient, such as in cholecystectomy, appendicectomy, gastric resection, bowel resection and liver resection [19]. Moreover, the use of drains might even be harmful for the patient, as it can slow down recovery and the restoration of bowel movements and can prolong the hospital stay or even cause postoperative complications such as retrograde intraabdominal infection, hollow organ perforation and/or loss of fluid and electrolytes.

Pancreatic surgery is different from surgery of hollow organs. Unlike enteric anastomotic dehiscence, which often presents with pneumoperitoneum and frequently causes peritonitis [20], pancreatic leak is more frequent, but the clinical course is not usually so dramatic [4]. Pancreatic leak or pancreatic fistulae can be easily diagnosed by analysing the amylase concentration in the drain effluent [21]. However, the amylase concentration is increased in the majority of patients on the first postoperative day, even in those patients who do not develop pancreatic fistulae in the postoperative course. This means that the pancreatic anastomosis is not ‘watertight’ in the majority of the patients [22].

The important question is whether any treatment adjustment in the postoperative course may prevent the development of clinically significant POPF. Recent studies have shown that intraabdominal drains and the manipulation with them are of great importance [11,13,23]. Three important questions arise when studying drains in pancreatic surgery:Is it necessary to use drains following pancreatic resection?When should the drains be removed?Which type of intraabdominal drain is most suitable?

These questions are addressed in turn in the subsections below.

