## Methods/Design

### Objectives and hypothesis

The aim of the DRAins in PAncreatic surgery (DRAPA) trial is to compare two types of intraabdominal drains in pancreatic resection and their effect on the development of POPF and postoperative complications. Closed-suction drains are more effective, as they remove fluid from the abdominal cavity under light negative pressure [13]. However, some surgeons believe that closed-suction drains represent a potential hazard to patients [33] and that negative pressure might increase the risk of POPF [13].

The following hypotheses will be tested:H0: The risk of development of POPF and postoperative complications is equal in both groups.H1: The risk of development of POPF and postoperative complications is different between the groups.

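### Any-grade POPF is read from drain fluid, so fluid yield and the number of amylase tests can differ by arm; grade B/C POPF and an equal-opportunity sensitivity analysis should be pre-specified

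*Protocol article*

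**What the plan says.** All places are in the Protocol article.

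- Primary and secondary endpoints: "The primary endpoint of this study is the rate of POPF occurrence". The case definition reads: "POPF is defined by the ISGPF as any measurable volume of drain fluid on or after postoperative day 3 with amylase content greater than" a threshold set at 3 × the upper normal serum level. Grades A, B and C all count. Grade A "has no clinical impact". The secondary endpoint is postoperative morbidity with a list of components, and grade B/C POPF is not on that list.
- Study treatment: "Amylase content in the drain fluid is analysed every other day starting on the third postoperative day until removal of the drain". Also: "Drains are removed between day 4 and day 6 after the surgery if no POPF develops". Nothing in the article says how the day within that window is chosen.
- Objectives and hypothesis: "Closed-suction drains are more effective, as they remove fluid from the abdominal cavity under light negative pressure".
- Minimizing systemic bias: surgeons, physicians and nurses cannot be blinded to the drain; outcome assessors are blinded.
- Minimizing measurement bias: POPF is detected and graded from the patient's record form. Blinding is called unnecessary because the patient cannot influence an objective endpoint.
- Background: "The important question is whether any treatment adjustment in the postoperative course may prevent the development of clinically significant POPF".

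**The concern.** The randomised device is also part of the measuring instrument. A grade A fistula exists only as raised amylase in drain fluid, and the article itself expects the two drains to differ in how well they remove fluid. A drain that yields nothing measurable cannot produce a grade A case.

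The chance of being found positive also depends on how long the drain stays in. That is decided by staff who know the arm, under no stated criterion. If removal day differs systematically by drain type, patients with the same biology are tested a different number of times.

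Either route could shift the any-grade rate in one arm without any change in the number of fistulas. This could hide a benefit of suction or suggest one that is not there. Because grade A has no clinical consequence yet counts in full, the reader of the result needs a pre-specified comparison of grades B and C to interpret it, and the listed endpoints do not include one.

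**Working it through.** **Tests per patient, from Study treatment.** Sampling falls on days 3, 5, 7 and so on while the drain is in place. A patient positive on day 3 is already a case. For a patient negative on day 3:

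- removal on day 4: one test (day 3);
- removal on day 5: one or two, because the order of sampling and removal is not stated;
- removal on day 6: two tests (days 3 and 5).

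Day 3 precedes the earliest permitted removal, so every drained patient has the same opportunity on that day.

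**The plan's own figure.** Sample size calculation gives 97 per group for 35% against 17.5%, a difference of 17.5 points. A two-sided 5% test with 80% power reproduces 97 (arcsine formula or t-test); the one-sided test named there gives 76 to 78. That mismatch is a separate matter. Here 97 per arm and a two-sided 5% test are used.

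**Size of the testing artefact.** Let q3 be the share positive on day 3, q5 the share of day-3 negatives who would be positive on day 5, and f the share of day-3 negatives who get the day-5 test. With identical biology in both arms:

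observed rate = q3 + (1 − q3) × q5 × f

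false difference = (1 − q3) × q5 × (difference in f)

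The article gives none of q3, q5 or f; all are assumptions. The 35% is the overall POPF rate, so at least 65% of patients would be negative on day 3, and 0.65 is a low value for 1 − q3.

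- Low: 0.65 × 0.05 × 0.40 = 0.013, or 1.3 points.
- High: 0.65 × 0.15 × 0.40 = 0.039, or 3.9 points.

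As a share of the planned effect this is 1.3/17.5 = 7% to 3.9/17.5 = 22%.

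**Effect on the false-positive rate at 3.9 points.** The standard error at a mean rate of about 33% is √(2 × 0.33 × 0.67 / 97) = 0.0675. The shift is 0.039/0.0675 = 0.58 standard errors. The rejection probability is Φ(0.58 − 1.96) + Φ(−0.58 − 1.96) ≈ 0.084 + 0.006 = 0.09, against a nominal 0.05.

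**Range over other assumptions** (q3 = 25-30%, q5 = 5-15%, pooled z-test, 97 per arm):

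| f in the two arms | False difference | Two-sided rejection |
|---|---|---|
| 0.9 vs 0.5 | 1.4 to 4.5 points | 5.5% to 10% |
| 0.8 vs 0.2 | 2.1 to 6.75 points | 6% to 17% |
| 1 vs 0 | 3.5 to 11.25 points | 8% to 40% |

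Even the extreme row stays below 17.5 points. The fluid-yield route is not quantified, because the article gives nothing to quantify it with.

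**Power for grade B/C.** Assume that 30-70% of the 35% are B/C and that suction halves the rate. The comparison is then 10.5% vs 5.25% up to 24.5% vs 12.25%. Two-sided power at 97 per group is 27% to 60%, and 80% power would need 413 down to 156 per group.

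**The case against.** Several points on the other side stand.

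- A reader might infer that POPF of every grade requires fluid from the randomised drain. The article does not support this. The case definition speaks of drain fluid without restricting it to that drain, and the descriptions of grades B and C mention new drains and CT-guided drainage. The dependence is clear for grade A only.
- A reader might infer from the Background that the trial cannot answer its own question. The aim, the hypotheses and the Discussion all refer to POPF without limiting the grade, and the Discussion gives comparability with other drain trials as the reason for the ISGPF definition. That is a legitimate reason to keep the any-grade primary.
- Severity and drain-independent outcomes are partly captured already: POPF is graded, intraabdominal collections are part of morbidity, complications are graded, and every patient has imaging before discharge. A drain that fails to evacuate may therefore show up as a collection.
- A sensitivity analysis and tables by arm are often left to an analysis plan, which is not shown here.
- The 40-point gap in day-5 testing has no support in the article.

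These points narrow the concern but do not remove it. Imaging is not part of the POPF definition. Assessors who work from the record form cannot change how many samples were taken, whether or not they are blinded. The argument for objectivity addresses influence by the patient, not by the device or the staff. The list of secondary endpoints is stated in the article, and grade B/C POPF is absent from it.

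**Conclusion.** The concern holds in a limited form. As written, the any-grade comparison is open to differential ascertainment: through fluid yield for grade A, and through one test or two for patients negative on day 3. Neither the direction nor the size of a bias can be derived from the article. A reader might take the figures above as evidence that the result will be biased; they show only what follows if removal day differs by arm. With 5-15% conversion on day 5 and a 40-point difference in day-5 testing, the artefact is about 1 to 4 points, and the two-sided false-positive rate rises to at most about 9-10%. Under none of the assumptions examined does removal timing alone produce the planned 17.5 points. This warrants a change to the endpoint set and the planned analyses, not a new primary endpoint.

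**What to change.** Keep any-grade ISGPF POPF as the primary endpoint and pre-specify, before any comparison by arm:

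1. Clinically relevant POPF (grade B or C, to 3 months) as a key secondary endpoint, reported as a risk difference with a 95% confidence interval.
2. A sensitivity analysis of the primary endpoint that takes the amylase criterion from the day-3 sample only.
3. A table by arm of drain removal day, number of amylase tests, and patients with no measurable fluid.

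The cost is wording. Grades, amylase, drain volumes and removal day are already collected, and no extra patients or samples are needed.

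The limits should be stated. Grade B/C has low power. The day-3 analysis omits fistulas that appear later and equalises test opportunity only, not fluid yield; the third item is there to make yield visible. Items 1 and 2 therefore support interpretation and should not be decision rules. In particular, requiring the B/C estimate to agree in direction before a claim is made would put too much weight on an imprecise estimate. No change to drain management is proposed.

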**Table 1 Tab1:** **Clinical parameters and postoperative complications for analysis**
^**a**^

**Parameters**	**Definitions**
Hospital stay	Days from initial operation to hospital discharge plus any readmission within 30 days
Operating time	Time from skin incision to wound closure (minutes)
Delayed gastric emptying	Failure to resume solid diet with prolonged need for nasogastric tube as defined by ISGPS [40]
Biliary leak	Bilirubin concentration in the drain fluid at least three times the serum bilirubin concentration as defined by ISGLS [38]
Postoperative haemorrhage	Evidence of blood loss from drains and/or nasogastric tube, based on ultrasonography, as defined by ISGPS [41]
Intraabdominal fluid collection	Collection of fluid measuring ≥3 cm associated with clinical or laboratory abnormalities
Symptomatic fluidothorax	Fluid in the pleural cavity associated with respiratory distress or a need to evacuate the fluid
Abdominal rupture	Dehiscence of abdominal closure with need for resuture of the laparotomy during the initial hospital stay
Myocardial infarction	Increase of serum concentration of CK-MB and troponin and/or the following ECG changes: new Q waves ≥0.04 in duration, new persistent ST elevation and/or depression
Pneumonia	Presence of a new infiltrate on chest X-ray, as well as the following: body temperature >38°C, abnormal elevation of WBC, or positive sputum, and requiring antibiotic treatment
Acute renal failure	Serum creatinine >3.0 mg/dl and/or need for dialysis
Wound infection	Surgical site infection associated with laparotomy that develops during the initial hospital stay
Urinary tract infection	Culture-positive urine, pyuria or bacteriuria on urinalysis requiring antibiotic treatment

^a^CK-MB, Creatine kinase MB isoenzyme; ECG, Electrocardiogram; ISGLS, International Study Group of Liver Surgery; ISGPS, International Study Group for Pancreatic Surgery; WBC, White blood cells.

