**Methods/Design:**

The aim of the DRAins in PAncreatic surgery (DRAPA) trial is to compare the closed-suction drain versus the closed passive gravity drain in pancreatic resection. DRAPA is a dual-centre, prospective, randomized controlled trial. The primary endpoint is the rate of postoperative pancreatic fistula; the secondary endpoint is postoperative morbidity with follow-up of 3 months.

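### Table 1 counts wound infection and abdominal rupture only during the initial hospital stay, although both belong to a morbidity endpoint with 3-month follow-up

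*Protocol article*

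**What the plan says.** The abstract (Methods/Design) sets the horizon: "the secondary endpoint is postoperative morbidity with follow-up of 3 months". The section on primary and secondary endpoints lists the components and refers to Table 1: "The secondary endpoint is the postoperative morbidity, including wound infection, intraabdominal collections, delayed gastric emptying, postoperative haemorrhage, pneumonia, abdominal rupture", followed by further items.

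Table 1 then closes the window at discharge for two of these components:

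- Wound infection: "Surgical site infection associated with laparotomy that develops during the initial hospital stay".
- Abdominal rupture: "Dehiscence of abdominal closure with need for resuture of the laparotomy during the initial hospital stay".

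No other complication row in Table 1 carries this limit. The hospital stay row of the same table looks past discharge: "Days from initial operation to hospital discharge plus any readmission within 30 days". Follow-up after discharge is planned in the section on postoperative data collection: "The patients will be seen by a clinical investigator 6 weeks and 3 months after the surgery in the outpatient department". The statistical methods section compares categorical secondary endpoints by chi-square or Fisher's exact test.

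**The concern.** There are two separate consequences.

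**Under-counting.** A wound infection that appears on day 20 in a patient discharged on day 12 falls within the declared follow-up but not within the Table 1 definition. A laparotomy resutured at a readmission on day 20 would add to hospital stay and to reinterventions, yet would not be an abdominal rupture. A result built on these rows cannot be described as 3-month morbidity for the two events.

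**Unequal observation time.** Discharge ends the window, and hospital stay is itself listed for analysis in Table 1. For Grade B fistula the endpoint section says: "Hospital stay is usually delayed, or readmission may be required". If one drain leads to more clinically relevant fistulae and so to longer stays, that arm is watched longer for wound infection and rupture. Chi-square and Fisher tests on simple proportions do not allow for this. A drain that shortened stay could then seem to reduce these events without doing so.

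**Working it through.** **1. Windows side by side.**

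| Item | Window | Place in the protocol article |
|---|---|---|
| Postoperative morbidity | 3 months | Abstract, Methods/Design |
| Wound infection | initial stay | Table 1 |
| Abdominal rupture | initial stay | Table 1 |
| Other complication rows | no initial-stay limit | Table 1 |
| Hospital stay | includes readmission within 30 days | Table 1 |
| Outpatient visits | 6 weeks, 3 months | Postoperative data collection |

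The mismatch follows from the text alone. The plan gives no figure of its own to reproduce, so what follows is illustration.

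**2. Inputs for the size.**

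- From the sample size section: fistula rates of 35% and 17.5%, a difference of 17.5 points.
- From the endpoint section: Grade A fistula does not delay discharge; Grade B usually does.
- Assumed, because the document is silent: base stay 12 days, 10 extra days per excess fistula, wound infection hazard 1% per day and equal in both arms.

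**3. Difference in mean stay.** 0.175 × 10 = 1.75 days, so 12 vs 13.75 days.

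**4. Counted infections with no true effect**, by 1 − exp(−hazard × stay):

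- 12 days: 1 − exp(−0.12) = 11.3%
- 13.75 days: 1 − exp(−0.1375) = 12.8%
- Spurious difference: about 1.5 points

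Giving the extra 10 days only to the excess fistula patients, instead of shifting the mean, leads to the same answer: 1 − exp(−0.22) = 19.7%, and 0.175 × (19.7% − 11.3%) = 1.5 points.

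**5. If half the excess is Grade A (assumed).** The mean difference is 0.0875 × 10 = 0.875 days. Then 1 − exp(−0.12875) = 12.1%, a difference of about 0.8 points.

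**6. Another onset model.** A constant 1% per day is usable only around the time of discharge; over 90 days it would give 1 − exp(−0.9) = 59%. As an alternative, assume a true 3-month rate of 15% in both arms and exponential onset with parameter m days, truncated at 90 days: F(t) = (1 − exp(−t/m)) / (1 − exp(−90/m)).

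| m (days) | Counted, 12-day stay | Counted, 13.75-day stay | Difference (points) | Missed at 12 days |
|---|---|---|---|---|
| 7 | 12.3% | 12.9% | 0.6 | 18% |
| 10 | 10.5% | 11.2% | 0.7 | 30% |
| 14 | 8.7% | 9.4% | 0.7 to 0.8 | 42% |

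The last column is 1 − F(12). It does not depend on any difference between arms. With a 3-month window and complete ascertainment, both arms would show 15%.

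**7. What larger effects would require.** A 4-day difference in mean stay needs 4 / 0.175 = about 23 extra days for every excess fistula; an 8-day difference needs 8 / 0.175 = about 46.

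**The case against.** The strongest reply has four parts.

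- **No shown difference in stay.** A reader might infer that the arm with more fistulae is necessarily watched longer and that the comparison is therefore biased. The document does not support that. The primary endpoint counts all grades, and Grade A does not delay discharge. Bias between arms needs a difference in Grade B or C fistula, or some other cause of longer stay. Without one, only under-counting remains. This stands.
- **Large effects are implausible on the plan's own figures.** A reader might picture mean stays 4 or 8 days apart. Step 7 shows how much each excess fistula would have to add. This stands too.
- **Late events are not all lost.** Data collection covers "hospital stay including readmissions for postoperative complications", together with reinterventions and the reasons for readmission, and the grading scheme in Table 2 has no in-hospital limit. Late events may therefore still be recorded there. It is too much to say that they vanish from the trial; they are missing from two named rows. Late wound infections treated without readmission remain the gap.
- **Borrowed definitions.** The endpoint section says that the complications are defined as in earlier publications. Whether the limit comes from those sources cannot be checked here. Borrowing would in any case not reconcile it with this trial's 3-month horizon.

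That the article is condensed is no answer: the limit is a stated rule, not an omitted detail.

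**Conclusion.** The point holds in a limited form. Table 1 contradicts the declared horizon for two named components of the secondary endpoint, and following it under-counts both events in those rows. Bias between arms is a conditional exposure, not an established fact: it arises only if length of stay differs by arm. Its size cannot be determined from the document. Under the stated assumptions it is about 1.5 points for wound infection, about 0.8 if half the excess is Grade A, and 0.6 to 0.8 under the alternative onset model. The under-count is likely to be the larger problem: 18% to 42% of events for a 12-day stay under that model, again on assumed inputs. Nothing was computed for abdominal rupture. The primary endpoint and the sample size are untouched. The change should be made, but the trial's main conclusion does not depend on it.

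**What to change.** In both Table 1 rows, replace the limit to the initial stay with one fixed window from surgery, the 3 months already stated for morbidity. Ascertain both events in hospital, at any readmission and at the 6-week and 3-month visits. Report in-hospital counts descriptively beside the 3-month counts.

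The cost is two table entries and one item on the record form at visits already planned. The downside is small but real. Patients are seen daily in hospital and only twice as outpatients, and late events would rest partly on history, so detection would still depend somewhat on length of stay. Labelling the two rows as in-hospital outcomes outside 3-month morbidity would remove the contradiction, but not the unequal observation time; it is the minimum, not the preferred change.

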## Discussion

Despite growing evidence in favour of pancreatic resection without intraabdominal drainage [13], routine elimination of drains cannot be recommended [25]. Rather more, drains could diminish the rate and severity of POPF in patients with high risk of POPF. Drains could possibly be avoided in patients with low risk of POPF [46]. However, the majority of pancreatic surgeons still consider routine placement of intraabdominal drains mandatory [15-17]. Once a decision is made to use intraabdominal drains, a controversy remains about which type of drain is most suitable in pancreatic resection [47]. Two types of drains are commonly used nowadays: passive gravity drains [26,30] and closed-suction drains [28,29]. Closed-suction drains are more effective, as they remove fluid from the abdominal cavity under light negative pressure [13]. However, some surgeons believe that closed-suction drains represent a potential hazard to patients [33] and that negative pressure might increase the risk of POPF [13]. No study conducted to date has specifically addressed the question of which type of drain is most beneficial for patients [12,13].

The DRAPA trial is designed to compare closed-suction drains with passive gravity drains in pancreatic surgery. Using the ISGPF definition of POPF will allow us to compare the results of this trial with those of other trials of drains in pancreatic surgery. This trial can show whether closed-suction drains represent hazards to patients or are beneficial in terms of decreasing POPF rates.

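### Table 1 counts wound infection only at the laparotomy, so infection at the drain exit site, the wound made for the randomised device, has no defined outcome of its own

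*Protocol article*

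**What the plan says.** Four places in the protocol article bear on the point.

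- **Table 1, wound infection row:** "Surgical site infection associated with laparotomy", counted only if it arises before the first discharge. The row limits both the site and the time window.
- **Study treatment:** "Drains are pulled through a separate stab incision outside the laparotomy and fixed with a stitch to the skin". A pancreaticoduodenectomy receives two drains. A distal pancreatectomy receives one, plus a second if the spleen is removed.
- **Primary and secondary endpoints:** "The secondary endpoint is the postoperative morbidity, including wound infection, intraabdominal collections, delayed gastric emptying, postoperative haemorrhage", followed by further items. Complications are also graded for severity with the scheme in Table 2.
- **Discussion:** "This trial can show whether closed-suction drains represent hazards to patients or are beneficial in terms of decreasing POPF rates".

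The Statistical methods section names chi-squared or Fisher tests for categorical secondary endpoints and a safety analysis set by treatment received. It lists no drain-specific event.

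**The concern.** The randomised intervention is the type of drain. Each drain makes its own opening in the skin, and that opening is the wound most directly tied to the intervention. The wound infection definition covers a different wound, the one made for the resection, which every patient would have whichever drain was used.

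What is at stake is the reading of one reported comparison. A result of no difference in wound infection would describe the laparotomy only. Because the article says the trial bears on hazard to patients, a reader could take that result as evidence about infection from the drains, which the row does not measure. Conversely, a real difference at the exit site would leave the row unchanged and would be spread across general morbidity grades.

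**Working it through.** No arithmetic applies: the point is a definition, and the documents give no exit-site infection rate. The check sets the sections side by side.

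1. **What laparotomy means in this article.** Study treatment uses the word for the incision, since the stab wound lies outside it. The abdominal rupture row of Table 1 also uses it for the incision, since it is what gets resutured. Reading the wound infection row in the same sense, it refers to the main incision.

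2. **Where the drain wound lies.** By Study treatment it is a separate incision outside the laparotomy. With steps 1 and 2 together, an infection there fails the site condition of the row.

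3. **Who is affected.** By the drain counts in Study treatment, every patient has at least one drain. With the 97 per group from the sample size section, 2 × 97 = 194 patients would each have at least one exit wound that the row does not cover. This is the number of patients with such a wound, not a number of infections.

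4. **Whether another row covers it.** Table 1 has rows for intraabdominal collection, haemorrhage, biliary leak, pneumonia, urinary infection and others. None describes infection of the skin or soft tissue at a drain exit.

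5. **Where such an infection could still appear.** The morbidity list is introduced as non-exhaustive, and it names neurological complications, which also have no Table 1 row, so Table 1 is not the whole set. Table 2 starts at any departure from an uneventful recovery. An exit-site infection could therefore be graded, for example Grade II if it needed antibiotics. But Table 2 grades by treatment needed or organ failure. It carries neither site nor cause, so the event would be one Grade II entry among all others.

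6. **Perforation.** The Background names, as possible harms of drains, "retrograde intraabdominal infection, hollow organ perforation and/or loss of fluid and electrolytes". Hollow organ perforation has no row of its own. Postoperative data collection does record reoperations, endoscopy, radiological procedures and reasons for readmission, so a perforation needing intervention would be seen, but as a reintervention and a grade rather than as a perforation.

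**The case against.** The strongest reply is that little is really lost. The morbidity endpoint is open-ended, Table 2 grades every complication, and Postoperative data collection includes imaging before discharge, inflammatory markers, reinterventions and daily drain volume. The one specific mechanism of harm given for suction is that "negative pressure might increase the risk of POPF", and fistula is the primary endpoint. The article is also a condensation: it takes definitions from cited sources, and the full protocol or record form may hold an exit-site item.

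Most of this stands, and it rules out several stronger readings.

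- A reader might infer that drain harms are left out altogether, or that the safety question cannot be answered. The documents do not support that. Fistula, collections and haemorrhage are compared, and other events enter through the grades.
- A reader might see a contradiction between the hazard motive for the trial and the Safety aspects statement that "no special training is necessary and no complications are expected". That sentence is about putting the drain in, not about its later effects, so there is no conflict.
- A reader might take the Background list of harms as differences expected between these arms. It describes the use of drains in general, both arms have drains, and the article ties frequent retrograde infection to open drains, which neither arm uses.
- A reader might want an estimate of the hidden difference. Any rates would be invented.

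What the reply does not remove is the printed site restriction. It is a stated rule rather than an omission through brevity, and a fuller record form would not change what this row counts. If it is argued that the row means the operation rather than the incision, the wording can be scored in two ways, which is also a reason to fix it.

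**Conclusion.** The point holds as a narrow flaw in one secondary outcome. As written, infection at the drain exit site is not counted as wound infection and can be seen only, without a label, within overall graded morbidity. This rests on reading laparotomy as the incision, the sense used elsewhere in the article.

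The size is total for the row, since all exit-site infections are excluded whatever their frequency, but unknown in events. The primary endpoint, the sample size and the overall morbidity comparison are not affected. It is a cheap improvement to what is compared between arms, not a defect that prevents the trial from addressing harm.

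**What to change.** Reword the Table 1 row to cover surgical site infection at the laparotomy or at a drain exit site, with the two sites recorded and reported separately. Compare each between arms with the chi-squared or Fisher test already named in Statistical methods. Apply the same diagnostic criteria to both sites, because the staff who inspect the exit wound can see which drain is in use.

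Record any hollow organ perforation as an event and compare it by arm. Do not ask treating staff to decide whether the drain caused it: they know the allocation, and a row for complications judged drain-related would import that knowledge. A broad row of that kind that also took in intraabdominal infection would overlap the collection row and the higher fistula grades.

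The cost is one or two more items on the record form and one more secondary comparison (two if perforation is tested), to be read as secondary. The daily visits already cover the window that the row sets, so no new procedure is needed. The laparotomy-only figure stays available for comparison with other reports. Recruitment was under way when the article was written, so the change should be dated, and exit-site infections in patients already enrolled should be sought in their records in the same way in both arms.
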